**Figure 1 figure1:**
[figure not shown]
Mobile Anxiety Sensitivity Program for Smoking and HIV (MASP+) participant enrollment flowchart. Note: after initial eligibility screening, participants will complete an enrollment call, baseline survey, randomization call, postrandomization survey, 6-week ecological momentary assessment (EMA) period, monthly check-ins for 5 months, and a final survey and week of EMAs at week 28. iCO: iCarbon Monoxide.

Persons deemed eligible at the enrollment call download the Insight app onto their personal smartphone or study phone. The Insight app houses the MASP+ content and is used to administer smartphone-based surveys and ecological momentary assessments (EMAs) to all participants. The study smartphones are provided to those without a smartphone and those with a smartphone that is incompatible with the Insight platform. Insight is supported on most Android smartphones (Android versions 6.0-14.0). Participants with a personal phone that is incompatible with Insight are sent a study phone. For those using their personal smartphone, the study staff instruct participants on how to download the app onto their personal phone. Insight adjusts according to the font size selected by participants on their phones. Participants who experience issues reading text in the app due to font size are instructed to increase font size in the phone settings. Once Insight is downloaded, participants are given a unique single-use code that enables them to use the app to complete the baseline assessment, which must be completed within 6 days after inputting the code. If participants do not complete the baseline survey within 6 days, they are no longer eligible to participate in the study. All participants are mailed a baseline package that includes a Bedfont iCO (iCarbon Monoxide) quit smokerlyzer, a Greenphire Mastercard, and NRT. The Bedfont iCO is used to biochemically verify self-reported abstinence at follow-ups.

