Upon completion of the baseline survey and receipt of the baseline package, the participants complete a randomization call with the study staff. During the randomization call, the participants are randomized to receive the MASP+ or QuitGuide interventions based on the randomization chart developed by the study statistician ([name]). Block randomization was used and stratified according to binary sex (assigned at birth). Variable-sized permuted block randomization (block sizes vary from 4 to 12) is used. Before data analyses, the balance of randomization will be checked and controlled for imbalanced factors by including any factors that differ between groups as covariates. The participants are provided with a unique code to access the app to which they are randomized. MASP+ participants have access to all MASP+ features (ie, Treatment Videos, Coping Toolkit, Quit Tips, and Stress Management Trainings) through the Insight platform. Participants randomized to the control intervention (ie, QuitGuide) have access to limited features (ie, App Instructions, Payment Tracking, Call Staff, and Record Stress) through the Insight platform and receive intervention content (ie, Track My Craving, Manage My Mood, and Learn To Quit) through the QuitGuide app. Participants assigned to the control intervention receive assistance with downloading the QuitGuide app through the Google Play Store. Both intervention groups use the Insight app to complete the study assessments, which include the baseline survey, weekly follow-ups, the 28-week follow-up, and EMAs. Once the code is entered, the research staff orients the participant to the app features and the iCO carbon monoxide (CO) breath testing device. Participants have access to MASP+ or QuitGuide content through the final follow-up (ie, the 28-week follow-up). At the end of the randomization call, participants are directed to take a brief postrandomization survey, which must be completed within 6 days after the randomization call. Failure to complete the postrandomization survey within 6 days does not affect participants’ status in the study.

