### Compensation

Each participant who enrolls receives a Greenphire Mastercard gift card that is loaded with compensation for survey completion. Participants receive all compensation in USD. Participants receive US $30 for completing the baseline assessment and US $10 for completing the postrandomization survey. Participants receive US $10 for completing each weekly follow-up assessment at weeks 1, 2 (quit date), 3, 4, and 5 as well as 6 weeks postbaseline (including the app-based survey, iCO breath test, and Zoom-based qualitative interview at week 6 only). Participants receive US $50 for completing the 28-week follow-up assessment (via Insight) and iCO breath test. Participants are compensated at the end of week 6 for EMA completion during weeks 1 to 6 and at the end of week 28 for EMAs completed during week 28. Specifically, participants receive a total of US $60 for completing 50% to 74% of the brief EMAs (4 per day×7 days=28 weekly EMAs) prompted during weeks 1 to 6, US $90 for completing 75% to 89% of EMAs, or US $120 for completing ≥90% of EMAs. For week 28, participants will receive US $10 for completing 50% to 74% of the brief EMAs, US $15 for completing 75% to 89% of EMAs, or US $20 for completing ≥90% of EMAs. Participants can use the “Payment” and “Weekly Survey Payment” buttons on the app’s home screen whenever desired to view an up-to-the-moment summary of EMAs presented and their current completion rate. Payments for completed EMAs are loaded onto participants’ Greenphire cards following week 6 and week 28.

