#### NCI QuitGuide Condition

The NCI’s QuitGuide app (available for free by request from the NCI Smokefree [58] server, on Google Play, or from the Google Play Store) is a free smartphone app that complies with many of the clinical practice guidelines for quitting smoking [54]. QuitGuide aims to orient smokers to their own smoking patterns and support users in developing the skills needed to quit smoking. Participants with a compatible smartphone who are randomly assigned to use QuitGuide are directed to download the app to their personal devices. Those who do not own a compatible device receive a study smartphone and are directed to download the QuitGuide app during the randomization call. Information explaining how to use the QuitGuide app is shared and reviewed during the randomization phone call. QuitGuide participants also download and use a modified version of the Insight EMA app with all MASP+ intervention features removed, which allows participants to receive EMAs and baseline or follow-up assessments. Refer to Table 1 for a list of QuitGuide features.

**Table 1 table1:** Comparison of treatment conditions^a^.

App components			MASP+^b^		QuitGuide
EMA^c^			✓		✓ (add on for this study)
Set a quit date			Quit date is set to 2 weeks after randomization		Quit date is set to 2 weeks after randomization
Share quit information on social media					✓
Smoking cessation psychoeducation			✓		✓
Content specific to Black smokers with HIV			✓		
NRT^d^ tips and use advice			✓		
AS^e^ psychoeducation			✓		

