#### Smoking Outcomes

During each weekly follow-up survey, smoking status is biochemically confirmed using the Insight platform and the Bedfont Scientific iCO smokerlyzer device. Biochemically confirmed 7-day point prevalence abstinence (PPA) at 26 weeks postquitting date is the primary study outcome. This is consistent with best practices as well as most published smoking cessation RCTs (refer to the clinical practice guidelines) [54,67]. In their baseline package, participants receive the Bedfont iCO smokerlyzer, which they use to verify smoking status at each weekly follow-up assessment (weeks 1-6 and week 26 postquitting date). At the end of each assessment, the participants are directed by the Insight app to connect the iCO device to the smartphone (simply by pressing the power button on the device) and complete the iCO test. The date and time of completion are collected and saved to our server along with the test results. Our CO criteria are informed by numerous studies that have used CO cutoffs of <7 ppm [68-74]. The CO level is a validated indicator of smoking status and outcomes and is strongly correlated with cotinine and other biochemical measures that have longer detection windows [75-77].

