#### Smartphone Training

Our team has developed and implemented a brief user-friendly training protocol to aid those with limited smartphone experience. During the randomization call, all participants, depending on condition assignment, receive training on how to use either the MASP+ app or the EMA-only Insight app and the QuitGuide app. Both versions of the Insight app (MASP+ and EMA only) contain an “App Instructions” button to remind participants of how each app feature functions (Figure 2). In previous studies, similar protocols have resulted in high EMA compliance rates (eg, 82%-87% of all EMAs completed) in samples of socioeconomically disadvantaged and nondisadvantaged adults [55,65,95,96]. All smartphones used in this study automatically collect data on intervention delivery (eg, number of times features are used and number of minutes treatment videos are watched).

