### Data Analyses

#### Overview

To test the hypothesis that MASP+ produces higher rates of smoking abstinence compared to the NCI QuitGuide app, a biochemically verified measure of 7-day PPA that is collected during weekly assessments via Bedfont iCO will be used. PPA is defined as no smoking, not even a puff, in the 7 days before follow-up assessments and biochemical verification of smoking abstinence (ie, CO levels <7 ppm according to an iCO test). We will calculate odds ratio effect sizes (with 95% CI) to estimate between-group differences for PPA at each follow-up assessment. The effect size for the comparison between conditions at the 26-week postquitting date assessment will serve as the primary analysis of the impact of treatment condition on smoking cessation.

We will then conduct a series of conditional latent growth curve models (LGM) to examine the impact of treatment condition on abstinence trajectories. First, an LGM will be specified using CO breath tests at 2 (quit date), 3, 4, 5, 6, and 28 weeks. The intercept of these models will be centered on the baseline assessment and will be specified to model linear change across the major assessments. A dummy code representing the treatment condition will be specified as a predictor of the intercept and slope factors to quantify the effect of MASP+ on the longitudinal course of abstinence.

The impact of treatment conditions on HIV quality of life, ART adherence, and HIV treatment engagement (hypothesis 2) will be examined using the same sequence of analyses: between-condition effect sizes followed by conditional LGM. We will then conduct univariate LGM to explore changes in AS a function of treatment (hypothesis 3), followed by a series of parallel process LGM to examine how changes in AS relate to changes in smoking and HIV outcomes. The indirect effects of treatment via AS will be evaluated by calculating bootstrapped CIs of the indirect effect using the MODEL INDIRECT command in MPlus.

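### MASP+ treatment and the primary and HIV outcome assessments share one app, while control treatment sits in a separate app; leaving the treatment app can cost the week-28 endpoint in one arm only

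*Protocol article*

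**What the plan says.** Recruitment and Procedures places treatment and measurement for the MASP+ arm in the same app: "The Insight app houses the MASP+ content and is used to administer smartphone-based surveys and ecological momentary assessments (EMAs) to all participants". Control participants "receive intervention content (ie, Track My Craving, Manage My Mood, and Learn To Quit) through the QuitGuide app", and under NCI QuitGuide Condition, "QuitGuide participants also download and use a modified version of the Insight EMA app with all MASP+ intervention features removed". Smartphone Training confirms that two versions exist: "Both versions of the Insight app (MASP+ and EMA only) contain an “App Instructions” button".

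Assessment runs through Insight in both arms: "Both intervention groups use the Insight app to complete the study assessments, which include the baseline survey, weekly follow-ups, the 28-week follow-up, and EMAs". Compensation repeats this for the endpoint visit: "Participants receive US $50 for completing the 28-week follow-up assessment (via Insight) and iCO breath test". Smoking Outcomes adds that, for the breath test, "the participants are directed by the Insight app to connect the iCO device to the smartphone". Under Data Analyses, Overview, "The effect size for the comparison between conditions at the 26-week postquitting date assessment will serve as the primary analysis" of the treatment effect on cessation.

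Event Sampling states that every MASP+ EMA ends with a treatment message and that control EMAs, otherwise identical, carry no tailored message. Data Loss Prevention says that staff can monitor EMA completion remotely and see who needs to be contacted.

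**The concern.** In the control arm, leaving the treatment and leaving the measurement are two separate acts on two separate apps. In the MASP+ arm, a participant who removes the treatment app removes the measurement app with it. Someone who stays only to answer EMAs still receives treatment content after each one. The chance of having a week-28 outcome could therefore depend on arm and on how well the treatment is accepted.

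At stake is the comparison at 26 weeks after the quit date. Sample Size Determination says that conclusions will rest mainly on effect sizes and confidence intervals, which are to guide later trials. A shift in the point estimate is therefore the relevant harm, more than any loss of power.

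**Working it through.** **Step 1. Follow each way of stopping through the stated procedures.**

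| What the participant does | MASP+ | QuitGuide |
|---|---|---|
| Ignores treatment features, keeps all apps | Week-28 survey and iCO test still available | Same |
| Deletes the app that holds the treatment | Insight is gone, and with it the only stated week-28 route | QuitGuide is gone; Insight and week 28 remain |
| Deletes Insight because of assessment burden | Week 28 lost | Week 28 lost |

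Only the second row differs between arms, and it is the whole of the point. The week-6 Zoom interview lies outside Insight, but it collects feedback rather than the primary or HIV outcomes.

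**Step 2. What the asymmetry could do to the primary odds ratio.** The article gives no dropout or abstinence rate, so there is no figure of its own to reproduce. Every rate below is an assumption: true abstinence p = 20% in both arms (no effect), missing m = 30% in MASP+ and 15% in QuitGuide.

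- Missing counted as smoking, missingness unrelated to abstinence: the observed rate is p(1 − m). MASP+ 0.20 × 0.70 = 14.0%; QuitGuide 0.20 × 0.85 = 17.0%. OR = (0.14/0.86)/(0.17/0.83) = 0.79.
- Completers only, everyone missing smokes: the observed rate is p/(1 − m). MASP+ 0.20/0.70 = 28.6%; QuitGuide 0.20/0.85 = 23.5%. OR = 0.400/0.308 = 1.30.
- Missing counted as smoking, everyone missing does smoke: 20% versus 20%, OR = 1.00.
- Completers only, missingness unrelated to abstinence: 20% versus 20%, OR = 1.00.

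The first two results each pair a handling rule with the mechanism under which it fails; the last two are the matching pairs. With 25% versus 15% missing, the two mismatched cases give 0.86 and 1.18. If the loss ran the other way (15% in MASP+, 30% in QuitGuide), they would be the reciprocals: 1/0.79 = 1.26 and 1/1.30 = 0.77. With equal missingness all four cases give 1.00.

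**Step 3. Model the coupling directly.** Assume 36 per arm (72 split equally), background loss c = 15% in both arms, a share q that stops using the treatment app in each arm, and a probability k that a MASP+ stopper also loses week 28 (zero for control stoppers). The expected number observed in MASP+ is 36(1 − c)(1 − qk); in control it is 36 × 0.85 = 30.6.

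- k = 0 (assessment fully separate): 30.6 in both arms, and the null OR is 1.00.
- k = 1: 24.5 observed in MASP+ at q = 20%, 21.4 at q = 30%, 18.4 at q = 40%.
- A middle case, q = 30% and k = 0.5, with abstinence 25% in those who keep using the app and 5% in stoppers: 26.0 versus 30.6 observed. Completers are 21.5% versus 19.0%, OR 1.17; with missing counted as smoking, 15.5% versus 16.2%, OR 0.95.

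Over q = 20–40% and k = 0.25–1, with abstinence 25% in continuing users and 5–10% in stoppers, or 20% in everyone, the null OR ranges from 1.00 to 1.63 in completers and from 0.55 to 0.99 with missing counted as smoking. The extremes need q = 40% and k = 1.

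**The case against.** The strongest reply is that the coupling bites only in a narrow case. Most MASP+ treatment sits behind optional home-screen buttons, so a participant can ignore it and still answer surveys. The embedded part is the message after each EMA, and EMAs run only in weeks 1 to 6 and in the week before the final follow-up. No message is described after the week-28 survey or the breath test. A control participant who tires of Insight and deletes it is lost as well, and that person manages two apps and gets no intervention content in return for four EMAs a day. Richer content might keep MASP+ users longer. Using EMA answers to tailor treatment is also part of what MASP+ is. All of this stands, so the direction of differential loss is open.

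A reader might infer that stopping MASP+ always means losing the endpoint, that MASP+ will have more missing data, or that counting missing as smoking necessarily penalises MASP+. The document supports none of these: ignoring features is not deletion, no attrition rate is given, and the penalty vanishes if those missing do smoke. Nor is it right that nothing can be recovered. Staff can contact low completers, payment rewards completion equally in both arms, and weekly readings exist up to the point of dropout. These measures soften the risk without removing the asymmetry, because none is described as collecting week-28 outcomes outside Insight.

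Withdrawal definitions and missing-data rules may stand in a full protocol or analysis plan that is not shown. Their absence is not part of this point, which concerns the collection route that the article does state.

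**Conclusion.** The point holds as a structural risk, not as a demonstrated bias. For a participant who abandons or deletes the app to stop the intervention, the week-28 survey and the CO reading are lost in MASP+ and kept in control. Under the assumed 30% versus 15% missingness, the null odds ratio lies anywhere from 0.79 to 1.30 depending on mechanism and handling rule, and it is 1.00 when the two match. Which case applies cannot be known without week-28 data on those who left, so an analysis rule chosen later cannot fully settle it. The size depends wholly on assumed rates, and the direction is unknown. This is a cheap improvement to data collection rather than a flaw that undermines the trial.

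**What to change.** 1. Offer any MASP+ participant who wants to stop the intervention a code for the existing assessment-only Insight version, so that surveys, iCO tests and the week-28 assessment continue as in control. App access is already assigned by code; whether a participant can be switched mid-trial needs confirming with the app team.
2. In both arms, send the week-28 smoking and HIV scales by REDCap link to anyone who has left Insight. REDCap is already used for the prescreener.
3. Record stopping treatment and stopping assessment as separate events, by arm, so that differential loss can be seen and described.

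The cost is protocol wording and the reuse of an app version and a survey platform already in hand; no treatment rule changes. At manuscript submission 9 of 72 participants were enrolled, so most would then still have been covered. The small downside is that a REDCap-only response has no CO reading. It can inform the HIV outcomes and sensitivity analyses, but not verified abstinence.

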### Compensation

Each participant who enrolls receives a Greenphire Mastercard gift card that is loaded with compensation for survey completion. Participants receive all compensation in USD. Participants receive US $30 for completing the baseline assessment and US $10 for completing the postrandomization survey. Participants receive US $10 for completing each weekly follow-up assessment at weeks 1, 2 (quit date), 3, 4, and 5 as well as 6 weeks postbaseline (including the app-based survey, iCO breath test, and Zoom-based qualitative interview at week 6 only). Participants receive US $50 for completing the 28-week follow-up assessment (via Insight) and iCO breath test. Participants are compensated at the end of week 6 for EMA completion during weeks 1 to 6 and at the end of week 28 for EMAs completed during week 28. Specifically, participants receive a total of US $60 for completing 50% to 74% of the brief EMAs (4 per day×7 days=28 weekly EMAs) prompted during weeks 1 to 6, US $90 for completing 75% to 89% of EMAs, or US $120 for completing ≥90% of EMAs. For week 28, participants will receive US $10 for completing 50% to 74% of the brief EMAs, US $15 for completing 75% to 89% of EMAs, or US $20 for completing ≥90% of EMAs. Participants can use the “Payment” and “Weekly Survey Payment” buttons on the app’s home screen whenever desired to view an up-to-the-moment summary of EMAs presented and their current completion rate. Payments for completed EMAs are loaded onto participants’ Greenphire cards following week 6 and week 28.

### Study Conditions

#### Both Conditions

Given that clinical guidelines recommend that all smokers attempting to quit should receive and use pharmacotherapy [54], both MASP+ and QuitGuide participants are sent NRT with their baseline package. Transdermal nicotine patches and nicotine lozenges are provided for use during the first 4 weeks postquitting date, and each participant is given the option order up to 4 weeks of additional NRT. For those in the MASP+ condition, an additional NRT can be ordered by clicking a button on the app home screen, which sends an encrypted email to the study team informing them of NRT requests. For those in the QuitGuide condition, NRT orders are placed by calling the number provided to participants and speaking with a member of the study team (Figure 2). In a prior study, 66% of enrolled participants used a similar app button or feature to place NRT orders [55]. Patches and lozenges were chosen for use in this study because of their safety and effectiveness (especially in combination with NRT), ease of use, and relatively benign side effects compared to other forms of NRT [56,57].

**Figure 2 figure2:**
[figure not shown]
Mobile Anxiety Sensitivity Program for Smoking and HIV (MASP+) app home screen. Note: app features include App Instructions, Treatment Videos, Coping Toolkit, Quit Tips, Stress Management Trainings, Order Patches/Lozenges, Record Stress, Record Cigarette About to Smoke, Record Cigarette I Already Smoked, Payment, and Weekly Survey Payment.

#### NCI QuitGuide Condition

The NCI’s QuitGuide app (available for free by request from the NCI Smokefree [58] server, on Google Play, or from the Google Play Store) is a free smartphone app that complies with many of the clinical practice guidelines for quitting smoking [54]. QuitGuide aims to orient smokers to their own smoking patterns and support users in developing the skills needed to quit smoking. Participants with a compatible smartphone who are randomly assigned to use QuitGuide are directed to download the app to their personal devices. Those who do not own a compatible device receive a study smartphone and are directed to download the QuitGuide app during the randomization call. Information explaining how to use the QuitGuide app is shared and reviewed during the randomization phone call. QuitGuide participants also download and use a modified version of the Insight EMA app with all MASP+ intervention features removed, which allows participants to receive EMAs and baseline or follow-up assessments. Refer to Table 1 for a list of QuitGuide features.

**Table 1 table1:** Comparison of treatment conditions^a^.

App components			MASP+^b^		QuitGuide
EMA^c^			✓		✓ (add on for this study)
Set a quit date			Quit date is set to 2 weeks after randomization		Quit date is set to 2 weeks after randomization
Share quit information on social media					✓
Smoking cessation psychoeducation			✓		✓
Content specific to Black smokers with HIV			✓		
NRT^d^ tips and use advice			✓		
AS^e^ psychoeducation			✓		
